# INSTITUTO MEXICANO DEL SEGURO SOCIAL

#### DELEGACIÓN ESTATAL EN GUANAJUATO

#### UNIDAD MÉDICA DE ALTA ESPECIALIDAD NO. 1 BAJÍO

**EFfect of**

**omega 3 acids ON OXIDATIVE STRESS in seropositive HIV patients**

**Abstract**

**Antecedents**: highly active antiretroviral therapy (HAART) has showed its effectiveness in the prevention of complications in seropositive HIV patients. However, they develop some manifestations such as lipodystrophy, dyslipidemia, and glucose intolerance increasing cardiovascular risk.

Epidemiological evidence on the benefits of fish oil and omega 3 fatty acid consumption has been accumulated over the past few decades. Clinical trials with fish oil have demonstrated a significant reduction in cardiovascular events. Omega-3 fatty acids are believed to be beneficial in prevention of atherosclerosis reducing lipids levels specially triglycerides in general populations and in patients on hemodialysis. Also in general populations it has been described a benefic effect of omega 3 acids on oxidative stress.

**Objetive**: to know the effect of omega 3 acids on different markers of oxidative stress in seropositive HIV patients.

**Methods**: We will perform a randomized parallel controlled clinical trial in seropositive HIV patients from 20 to 55 years old on clinical score A1, A2, B1 or B2 who received HAART. Exclusion criteria will be diabetes mellitus, hypertension, use of hypolipidemic agents,dyslipidemia identified before receiving HAART therapy, and use of protease inhibitors. They will be randomly assigned to receive omega 3 fatty acids 2.4 g (Zonelabs, Marblehead MA)or placebo for 6 months. At baseline anthropometric measurements will be performed. After at least 8 fasting hours a venous 20 ml blood sample of will be obtained to measure lipid profile, glucose and stress oxidative levels (nitric oxide, malondialdehyde, total glutathione and lipid peroxidation products).

Sample size was calculated according to different variables. For example for malondialdehyde we consider a previous study in patients on hemodialysis (22) where after 2 months of omega 3 fatty acids treatment, a difference of 0.9 nmol/l was found between groups, with a SD=0.9 and 0.7 nmol/l in the treatment group and in the control group respectively. Whit this information we obtained a sample size of 17 patients per group for an 80% statistical power with α= 0.05. Similar sample size was calculated for glutathione considering a difference=500 µg/l between groups and SD=700 µg/l (48). Whit this information we obtained a sample size of 31 patients per group for an 80% statistical power with α= 0.05. For nitric oxide we calculated a sample size of 30 patients per group considering a difference in 25% in its levels between groups and SD=10µmol/L with similar statistical power and α value (49). Assuming a 15% patient lost, a sample size of 35 per group was considered.

**Resources and infrastructure*:*** In our hospital, enough number of HIV+ patients receives medical attention to reach the sample size in a mean period of a year. All clinical determinations are factible to perform in the CIBO in Jalisco state. We will compete for funding to obtain laboratory reagents and drugs.

**Experience of the group**: The working group is composed of researchers with experience in the pharmacological management and complications of these patients and in research methodology. Several publications of some researchers have proven oxidative stress in various pathologies.

**Time to develop**: Once registered with the National Commission of Research, we will compete for resources and will start the protocol to complete the sample size and follow-up of patients.

**Antecedents**

In Mexico, as in other countries, the Acquired Immune Deficiency Syndrome (AIDS) has become a very complex priority public health problem that threatens national security and for economic and social development nations. Mexico is classified as a country with a concentrated epidemic of AIDS, characterized by a prevalence of HIV infection has spread rapidly in one or more subsets of the population, but is not yet established in the general population. In this type of epidemics, HIV prevalence has remained constant over 5% in at least one subgroup of the population, and among pregnant women in urban areas is less than 1% (1).

The AIDS epidemic in Mexico is concentrated in some populations at higher risk, such as sex workers (men) with a mean prevalence of 15%. Then men who have sex with men (11%), injection drug users (5%), sex workers (2%) and persons deprived of liberty (1%). Clients of sex workers and heterosexual men and women report significantly lower prevalence. According to estimates by the National Center for the Prevention and Control of AIDS (CENSIDA), together with UNAIDS, in Mexico there are 220,000 adults living with HIV (2009), of which 60% are men who you have sex with men (MSM), 23% of heterosexual women and 6% for clients of sex workers, primarily heterosexual (1). By 2010, the same source cites national 144.127 cumulative AIDS cases with an incidence of 133 patients per 100,000 inhabitants, being the most affected age groups of 15 to 44 years of male dominance (82.18%) (2).

Before the arrival in Mexico of antiretroviral treatment, the overall death rate from AIDS was 1.8 deaths per hundred thousand inhabitants in 1990 and peaked in 1996 with 4.8 deaths registration. From that last year, progressive access to a new group of antiretroviral drugs known as protease inhibitors (PI) radically changed the prognosis of patients with HIV / AIDS. It has been shown that the combination of drugs known as highly active antiretroviral therapy (HAART by its acronym in English), slows the damage of the immune system and substantially improve the quality of life (1).

However, these benefits have been overshadowed by the emergence of new side effects as effective treatment, including highlights its deleterious effect on lipoprotein metabolism. This is characterized by elevated levels of very low-density lipoprotein and triglycerides, elevated total cholesterol, low density lipoprotein and decreased levels of high density lipoprotein. Triant compared rates of myocardial infarction in two hospitals in Boston with more than 3,800 patients, and reported a significantly higher rate in HIV + compared to HIV negative, in addition to a higher prevalence of risk factors such as hypertension, diabetes mellitus and dyslipidemia (3).

HAART has shown its effectiveness in preventing complications of the disease and increase survival (4). Furthermore, it has been reported that 20% of patients undergoing HAART developed lipodystrophy after 12 months of treatment, 2% diabetes mellitus and 25% dyslipidemia (which was as high as 41% in case of low HDL-cholesterol) at 15 months of treatment (5).Lipodystrophy is characterized by changes in the distribution of body fat (fat accumulation in the central region of the body especially the trunk, abdomen and dorsocervical peripheral region accompanied by atrophy of subcutaneous fat, dyslipidemia and insulin resistance) (6 7), which also increases the risk of cardiovascular disease by participating in the process of atherosclerosis (8).

Atherosclerosis is a chronic inflammation syndrome with predilection on artery walls. In the initial phase of development of this syndrome, low density lipoprotein (LDL) and other pro-inflammatory proteins stimulate the expression of adhesion factors of endothelial cells and growth factors that attract circulating monocytes to endothelial cells penetrating the intimate where colony stimulating factors induce macrophage differentiation of monocyte-macrophage. Macrophage uptake of oxidized LDL cholesterol promotes their further evolution into foam cells, important players in atherosclerosis development. Then, activation of T cells, proliferation of smooth muscle cells and deposition of extracellular matrix are produced in the vascular intima. These molecules interact with deposits in the intima producing necrosis, causing the formation of fibrous plaques containing a core of lipid and a fibrous layer formed of smooth muscle cells and matrix. Eventually the progressive growth of plaque rupture can reach the blood stream and cause stenosis or closure of the lumen of other arteries. Furthermore, as a result of plaque rupture, platelet activation generates thrombosis obstruction of blood flow resulting in acute myocardial ischemia or cerebral vascular disease. Then, atherosclerosis is a dynamic process and one of its main triggers is oxidative stress (9).

**Oxidative stress**

Oxidative stress is defined as a situation where there is an increase in the rate of generation of oxidative species and free radicals (FR) and a decrease in the activity of the defense systems, resulting in higher concentrations at steady state active of oxygen species. In these situations, the toxic effects of FR result in chemical reactions on lipids, proteins, carbohydrates and DNA, which may result in irreversible damage and even cell death (10).

There are numerous diseases that have been associated with this imbalance between oxidants and antioxidants: atherosclerosis, cancer, porphyria, cataracts, iron and copper overload, Parkinson's disease, Alzheimer's disease, diabetes, etc. (10).

One of the biggest contributors of oxidative stress is the family of molecules reactive oxygen species (ROS). These include free radicals such as superoxide anion (O2-), hydroxyl radical (HO-), lipid radicals (ROO) and nitric oxide (NO). Other reactive oxygen species, such as hydrogen peroxide (H2O2), peroxynitrite (ONOO-) and hypochlorous acid (HOCl), although they are not free radicals, have oxidizers effects that contribute to oxidative stress. ROS have been implicated in cellular necrosis and apoptosis damage due to its direct oxidizing effects on macromolecules such as lipids, proteins and DNA (11-12). Reactions between FR and polyunsaturated fats in the cell membrane can result in peroxyl acid radicals that accumulates in the cell membrane disrupting protein function and signal transduction. Under oxidative stress, the superoxide ion release free iron of various molecules to produce highly reactive hydroxyl radicals by the Fenton reaction with hydrogen peroxide (13). ROS also induce the opening of the permeability transition pore mitochondrial membrane and release of cytochrome C and other factors that may cause apoptosis (14-15). The O2- radicals can also interact with nitric oxide (NO) signaling, resulting in the formation of reactive nitrogen species (RNS) that reduce the bioavailability of NO causing "nitrosative stress" toxicity (16). Excessive production of RNS results in nitrosylation reactions changing the structure of proteins with loss or change of their functions (17).

Moreover, it has been shown that increased oxidative stress is attached to the HIV infection. Canadian researchers suggested that a weak antioxidant defense system is a significant factor when considering the high oxidative stress observed in the population infected by the virus*.* The increased production of reactive oxygen molecules might stimulate the replication of HIV and related immunodeficiency (18).

ROS are a staple in antimicrobial defense and antitumor. Oxidative stress is recognized associated with the pathophysiology of several diseases. Experimental evidence links the process of oxidative stress in the development of viral diseases such as infection by human immunodeficiency virus (HIV) (19).

Under physiological conditions the cells increase their activity of antioxidant enzymes and other defenses to balance oxidative stress (20-21). These include manganese dependent superoxide dismutase (Mn-SOD), superoxide dismutase copper / zinc (Cu / Zn SOD), glutathione peroxidase, glutathione reductase and catalase (CAT). Other antioxidant defenses include "scavengers" of free radicals as vitamin E, beta carotene and vitamin C (EO4) and recently the participation of omega 3 fatty acids has been also considered as antioxidants (22).

**Oxidative stress in HIV+ patients**

The first evidence of the presence of EO in these individuals was reported in 1988 with an increase of malondialdehyde (MDA) as an index of oxidative damage in HIV-positive patients compared with a group of healthy individuals, and in 1989 in HIV-positive individuals, deficiency of systemic glutathione (GSH) was reported (19).

The relationship between infection with human immunodeficiency virus (HIV), nutrition and immune function is complex. The effect of HIV infection on nutritional status is unclear; however the effect of nutritional status on the infection has not been adequately evaluated (23).

The OE has been considered a cofactor in the progression of HIV infection to AIDS condition, associated with an increase in viral load and the decrease in CD4 + T cells (apoptosis) producing a depression in the immune response (19).

**Omega 3 fatty acids**

Omega 3 fatty acids are essential fatty acids, because the body cannot manufacture them from other substances and belong to the group of polyunsaturated fatty acids. It is estimated that the ideal ratio between these two types of fatty acids to include in our diet could be 4 parts omega 3 and 1 part omega-6 fatty acids.

Recently in JELIS (24) study that followed-up patients for five years, it was reported that those Japanese patients with dyslipidemia who received 1800 mg of eicosapentaenoic acid (C20: 5n-3, EPA) per day alone or in combination with statins, reduced event rate of major cardiovascular disease. Also the results of the study "GISSI Prevenzione" reported reduced risk of sudden death from 4 months post-infarction with the use of EPA and docosahexaenoic acid (C22: 6n-3, DHA), and this effect remained in the 3.5 years of follow-up (25). Other mechanisms proposed by lowering cardiovascular risk in people with dyslipidemia are their hypotensive effect, (26) vascular relaxation, (27) and increased heart rate variability (28). In hypertensive rats, DHA treatment for 6 weeks reduced the vascular wall thickness of the coronary artery and aorta (29). Also in humans, atherosclerotic plaques of patients undergoing carotid endarterectomy, who received Ώ-3 for ~42 days showed less macrophages infiltration compared with control group and were more resistant to rupture (30). The European and American cardiology societies have included EPA and DHA in the new treatment guidelines for myocardial infarction (31).

Ώ-3 fatty acids ‘doses for multiple outcomes varied between studies. For example, Freeman reported decrease in the level of postpartum depression after 8 weeks with 2.8 g per day of EPA + DHA (32). Geelen et al. (33) demonstrated that 14 weeks of a moderate dose (1,260 mg / day) reduced the heart rate in patients with complex ventricular arrhythmias and based on the GISSI-HF study (34) for heart failure has been established recommendation of use 800-1,000 mg / day of EPA / DHA in patients at high cardiovascular risk (34-35). Moreover, in patients with hypertriglyceridemia it has been reported that it is safe to administer even dose 4g / day of Ώ-3 fatty acids combined with other lipid-lowering therapies such as statins, fibrates and niacin (36-39). Even the American Heart Association supports the dose of 1g / day of EPA and DHA in combination in patients with documented cardiovascular disease (40). Because adverse effects have been reported more frequently in doses from 4 g and its effectiveness is demonstrated on average from 1 g, we decided to study an intermediate dose of 2.4 g (41-42).

Although details of the cellular mechanism by which these acids lower serum triglycerides are unknown, EPA and DHA can reduce VLDL synthesis (43), increased triglyceride clearance of VLDL (44) and increase the conversion remnants of VLDL to LDL (45). In a recent study in patients undergoing hemodialysis, supplementation with omega-3 increased levels of antioxidants factors such as glutathione peroxidase and superoxide dismutase after two months of treatment, and decreased levels of malondialdehyde, improving oxidation state (22).

The safety and efficacy of omega-3 fatty acids for the treatment of hypertriglyceridemia in the general population is well documented (45-46). In addition to the "fishy taste", adverse effects are alterations in intestinal transit, and it has been reported that reduces the generation of thrombin independently of vitamin K (41), but not increases bleeding risk (42). Even in patients receiving other coumarin anticoagulants and antiplatelet agents, has not been observed increase in the rate of bleeding episodes that required decrease anticoagulant dosage (47).

**Justification**

An antioxidant therapy in combination with antiretrovirals may benefit HIV-infected patients, extending and improving their quality of life. This could significantly reduce oxidative stress which is a trigger for several related diseases such as diabetes mellitus, hypertension and cardiovascular disease in general.

The use of omega-3 as complementary treatment opens the possibility to reduce cardiovascular risk by reduction of oxidative stress in these patients without drug interactions observed with the use of statins.

**Problem identification**

What is the effect of using omega-3s on various markers of oxidative stress in HIV+ patients?

**PRIMARY OBJECTIVE:** to know the effect of omega 3 acids on different markers of oxidative stress in HIV+ patients.

Change on malondialdehyde, nitric oxide and glutathione levels after treatment with omega 3 acids for 6 months compared with placebo

**Ha**: use for 6 months of omega 3 fatty acids, reduce oxidative stress in HIV+ patients.

**Ho**: use for 6 months of omega 3 fatty acids; do not reduce oxidative stress in HIV+ patients.

**Material and methods**

**Type of study**

Randomized, parallel, controlled clinical trial, doble blind.

**Universe of the study**

HIV-positive patients attending the AIDS Medical Unit of High Specialty Bajio, IMSS, in the service of Infectious Diseases, in the city of Leon, Guanajuato, Mexico.

**Sample size**

It was calculated according to different variables. For example, for malondialdehyde we consider a previous study in patients on hemodialysis (22) where after 2 months of omega 3 fatty acids treatment, a difference of 0.9 nmol/l was found between groups, with a SD=0.9 and 0.7 nmol/l in the treatment group and in the control group, respectively. With this information we obtained a sample size of 17 patients per group for a 80% statistical power with α= 0.05. Similar sample size was calculated for glutathione considering a difference=500 µg/l between groups and SD=700 µg/l (48). With this information we obtained a sample size of 31 patients per group for a 80% statistical power with α= 0.05. For nitric oxide we calculated a sample size of 30 patients per group considering a difference in 25% in its levels between groups and SD=10µmol/L with similar statistical power and α value (49). Assuming a 15% patient lost, a sample size of 35 per group was considered by t test for sample size (50).

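### With the assumed 15% loss, 35 per group leaves about 30 evaluable against the 31 that glutathione needs, so its power is about 77–79%, not 80%

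*Protocol*

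**What the plan says.** The Sample size section of the protocol works through three markers, and the abstract repeats the same figures.

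- **Malondialdehyde:** difference 0.9 nmol/l, SDs 0.9 and 0.7, giving 17 per group.
- **Glutathione:** difference 500 µg/l, SD 700 µg/l. The result is "With this information we obtained a sample size of 31 patients per group for a 80% statistical power with α= 0.05".
- **Nitric oxide:** "For nitric oxide we calculated a sample size of 30 patients per group considering a difference in 25% in its levels between groups", with SD 10 µmol/L and the same power and alpha. No reference mean is given for the 25%.

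The section ends: "Assuming a 15% patient lost, a sample size of 35 per group was considered". It attributes the 35 to a t-test calculation and cites a textbook chapter. It states neither the formula used to allow for loss nor the marker on which the 35 is built.

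All three markers are named under the primary objective (Problem identification). The Statistical analysis section plans an unpaired t test, or a Mann–Whitney test for non-normal variables, at p < 0.05.

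**The concern.** The per-marker figures are the numbers that must be analysed to reach 80% power. The planned size should therefore still leave the largest of them, 31, after the assumed loss. It leaves slightly fewer, so the protocol's size, loss assumption and power for glutathione cannot all hold together.

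What is at stake is how a null glutathione result would be read. It would be set against a stated 80% that the design, on its own assumptions, does not quite reach. Any reader can find the mismatch from the printed figures.

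**Working it through.** **Inputs (Protocol, Sample size).** Glutathione difference 500 and SD 700; power 80%; alpha 0.05; loss 15%; 35 per group. Equal allocation is implied by the equal group sizes. Sidedness is not stated. I take two-sided, because it reproduces 31, whereas one-sided gives 25.

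**1. Reproduce the plan's 31.** Normal approximation:

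n = 2 × (1.96 + 0.8416)² × (700/500)² = 30.8, rounded up to 31.

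The stated figure is confirmed. The t-test calculation gives 31.8, rounded up to 32. With 31 per group, power is 80.3% by the normal approximation and 79.0% by the t test.

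**2. Evaluable patients after the assumed loss.**

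35 × 0.85 = 29.75 per group, which is 1.25 below 31 and 0.25 below 30.

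In whole patients, 15% of 35 is 5.25. Losing 5 (14.3%) leaves 30. Keeping 31 of 35 would allow a loss of only 1 − 31/35 = 11.4%.

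**3. Size that would be consistent.**

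| Starting requirement | n / 0.85 | n × 1.15 |
|---|---|---|
| 30 (nitric oxide) | 35.3, so 36 | 34.5, so 35 |
| 31 (glutathione) | 36.5, so 37 | 35.65, so 36 |
| 32 (glutathione, t test) | 37.6, so 38 | – |

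Division by 0.85 is the correct step, because it returns the required number after loss: 37 × 0.85 = 31.45 and 38 × 0.85 = 32.3.

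**4. Glutathione power after the assumed loss.** The standardised difference is 500/700 = 0.714. By the normal approximation, power = Φ(0.714 × √(n/2) − 1.96).

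| Evaluable per group | Normal approximation | t test |
|---|---|---|
| 29.75 | 78.7% | 77.3% |
| 30 | 79.0% | 77.6% |
| 31 | 80.3% | 79.0% |

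By the t test, the shortfall from 80% at 29.75 is 2.7 points. Of these, 1.0 point comes from using 31 where the t test needs 32, and 1.7 points come from the loss step. By the normal approximation the shortfall is 1.3 points.

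**5. The other two markers.**

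- **Nitric oxide:** power cannot be computed directly without a reference mean. Assume that 30 per group gives exactly 80%. That implies a difference of 10 × (1.96 + 0.8416) × √(2/30) = 7.2 µmol/L, and power at 29.75 is then 79.7%.
- **Malondialdehyde:** with the larger SD of 0.9 the standardised difference is 1. Power at 29.75 is 97.1% by the normal approximation and 96.6% by the t test. With the pooled SD it is about 98.8%.

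**The case against.** The strongest reply is that this is too small to matter. The planned size is within two or three patients per group of the consistent figure. By the method that reproduces 31, the power loss is 1.3 points, and the inputs are less certain than that: an SD of 688 instead of 700 would restore 80% at 29.75, since 500 × √(29.75/2) / 2.8016 = 688. By the t test an SD of about 677 would do so. This stands as an argument about severity. It does not remove the inconsistency, because the protocol fixes the SD at 700.

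It can also be said that the t-test figures are unfair to a plan whose 31 comes from the normal approximation. That is partly right, and is why both methods are shown. But the section itself refers to a t test and the planned analysis is a t test, so neither method can be set aside. Both fall below 80%.

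Four stronger readings are tempting, and the protocol does not support them.

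- **The glutathione requirement was left out.** A reader might infer this because 30 × 1.15 = 34.5 rounds up to 35. But 31 × 1.15 = 35.65 also gives 35 if truncated. No formula is stated, so the cause is unknown.
- **Only 29 per group remain, so power is about 76%.** Reaching 29 takes six losses, or 17.1%, which is more than the plan assumes.
- **Nitric oxide is underpowered too.** The gap is a quarter of a patient, and the power figure rests on a back-calculated difference.
- **Power is far lower after correction for three markers.** The protocol specifies no such adjustment. Whether it should is a separate question.

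**Conclusion.** The point holds as a minor internal inconsistency. On the protocol's own inputs, 35 per group with 15% loss gives about 30 evaluable. Glutathione power is then about 77–79%, roughly 1 to 3 points under the stated 80%. Nitric oxide is at about 80% and malondialdehyde is above 95%.

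The conclusion assumes two-sided alpha of 0.05 without adjustment, equal groups, the stated difference and SD for glutathione, and, for nitric oxide, that 30 per group gives exactly 80%. It does not show that the trial is materially underpowered, and it does not call the design into question.

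**What to change.** Keep 35 per group and correct the closing sentence in both the abstract and the Sample size section, for example:

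> With 15% loss about 30 per group are evaluable, giving about 77–79% power for glutathione, about 80% for nitric oxide and over 95% for malondialdehyde at two-sided 0.05, unadjusted.

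The nitric oxide reference mean should be added so that its figure can be checked. If the mean is not available, the text should say that the 80% is taken from the stated 30 per group.

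This costs one sentence in two places and a slightly less favourable power for one marker. No extra patients are needed, and conduct and analysis do not change.

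If 80% for glutathione is to stand, the consistent size is 37 per group (74 in total instead of 70), or 38 per group (76 in total) using the t-test requirement of 32.
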